## Abstract

Postnatal depression affects 10-15% of women worldwide (Cox, Murray, & Chapman, 1993). This randomised feasibility study investigates whether using an infant carrier leads to reductions in postnatal depression scores, increased wellbeing scores, and changes in parenting experiences. Maternal attachment style is examined as a potential moderator of this effect. Mothers of infants aged 0-6 weeks will be randomised to receive sling training and free sling hire, either immediately, or after a wait list period of 12 weeks (the control group). This study aims to collect information regarding the feasibility of recruitment and administering the intervention for future Randomized Control Trials.

## Introduction

Worldwide, 10-15% of mothers suffer from postnatal depression (PND)(Cox et al., 1993), a form of depression where onset occurs soon after childbirth (Di Florio & Jones, 2018).

An even greater percentage of mothers (around 30%) may experience subthreshold depressive symptoms following childbirth. (Kingston et al., 2018). There is a need for low intensity interventions to mitigate these symptoms, and support mothers' well-being.

### *Biopsychosocial Perspective on PND*

As with other depressive disorders, the biopsychosocial model (Engel, 1977) may be used to conceptualise the causes and maintaining factors of postnatal depression. This model proposes that biological, psychological and social factors are all interlinked and important in causing and maintaining illness (McInerney, 2002). Biologically, associations have been found between the functioning of the endocrine (hormone), immune and neurotransmitter systems, and the occurrence of PND (Harris, 1994).

Psychologically, women with PND tend to experience negative thoughts about themselves and specifically their ability to parent (Milgrom & McCloud, 1996). Negative patterns of thinking are key to the development and maintenance of depression (e.g. Beck's "cognitive triad"; Beck, 1967). Cognitive-based therapies typically involve building evidence that challenges negative thinking (Beck, 1979).

Finally, social isolation and social engagement are risk and protective factors, respectively, for depression (Thoits, 1985), including PND (Nielsen, Videbech, Hedegaard, Dalby, & Secher, 2005).

National Institute for health and Care Excellence (NICE) guidelines recommend psychotropic medication or high-intensity psychological interventions for those with moderate to severe PND (NICE, 2014). For those with mild to moderate symptoms, NICE recommend seeking healthy lifestyle advice, self-help programmes, computerised behavioural therapy, or exercise programmes (NICE, 2009). These various interventions may be onerous for mothers to access soon after giving birth (Bigelow, Power, MacLellan-Peters, Alex, & McDonald, 2012).

Evidence is emerging for alternative early intervention methods, including psycho-educational home visits (Ammaniti et al., 2006), parenting groups (Puckering, McIntosh, Hickey, & Longford, 2010), and baby massage (Onozawa, Glover, Adams, Modi, & Kumar, 2001), but these are not yet well-supported.

A low cost, low intensity intervention known to have beneficial effects on both maternal and infant wellbeing is close body contact (Winberg, 2005). Bigelow et al. (2012) found that mothers who provided regular skin-to-skin contact for the first month of their infant's life had lower depression scores than mothers in a control condition who provided little or no skin-to-skin contact.

One way in which a mother may increase close body contact with their infant, which may have similar benefits as skin-to-skin, is through the use of a "baby sling". This is a structured piece of fabric that allows the parent to carry their infant against their body (McGhee, n.d.).

Drawing from biopsychosocial models of depression, there are several mechanisms by which sling use might positively affect PND and maternal wellbeing.

*Biological: Hormonal Effects*

Close body contact between a mother and infant, such as that promoted by sling use, promotes the release of oxytocin in the mother (Uvnäs-Moberg & Prime, 2013). Oxytocin may reduce symptoms of those mental health difficulties which involve impaired social functioning, including depression (Cochran, Fallon, Hill, & Frazier, 2013; Domes, Normann, & Heinrichs, 2016).

*Social: Autonomy and Social Support Effects*

Self-determination theory notes that the absence of autonomy can lead to mental health difficulties (Deci & Ryan, 2008). Sling use allows the mother to have her hands free, and thus travel and carry out daily activities while holding her infant in close body contact (Blois, 2005). Sling use may therefore positively impact upon maternal wellbeing by providing this increased freedom and improving mothers' sense of autonomy, which in turn could reduce the risk of social isolation.

Additionally, sling use provides access to a range of social networks built around using slings (e.g. facebook groups and social meetings). Therefore sling use may also increase mothers' social opportunities and engagement.

*Psychological: Infant-parent Relationship and Interaction Effects*

An infant's attachment to the mother may contribute to the mother's experience of parenthood. For example, insecurely attached infants may cry more often than those who are securely attached to their parent (Belsky, Rovine, & Taylor, 1984).

Anisfeld et al., (1990) found that sling use may promote secure attachment in infants. Related to this, carrying has been found to reduce infant crying (Hunziker and Barr, 1986). Therefore, sling use may lead to a more positive parenting experience, building the number of positive interactions they experience, and consequently increasing feelings of parental self-efficacy (Jackson, 2000).

Altogether, by supporting each of these biopsychosocial factors, sling use may have a positive effect on symptoms of PND in mothers of young infants.

Parental “attachment style”, which refers to how the person approaches relationships later in life (Jones, Cassidy, & Shaver, 2015), may moderate the relationship between sling use and postnatal depression.

Parents with different attachment styles appear to differ in their thoughts and feelings about parenting (Millings, Walsh, Hepper, & O’Brien, 2013; Rholes, Simpson, & Friedman, 2006) and also about close physical contact (Posado, Waters, Crowell & Lay, 1995; Simpson, Rholes & Nelligan, 1992). Thus mothers with different attachment styles may respond differently to interventions for PND which involve such contact.

The aim of this study is to be the first to examine whether sling use may have a positive impact upon symptoms of postnatal depression, and furthermore, whether parental attachment style mediates this relationship.

Ideally, a randomised control trial (RCT) design would be used to establish a causal relationship between sling use and reduced occurrence of postnatal depression (Cartwright, 2010). To the researchers’ knowledge, there has not yet been an RCT that examines the impact of sling use on the parent specifically. However, before investing time and resources in a full-scale RCT, it is important to know whether it is possible to study the impact of this intervention (sling use) upon this population (mothers of young infants). In particular, it is anticipated that there may be challenges around recruitment and treatment fidelity.

For these reasons this study is a feasibility study, gathering information which may be used to estimate parameters (e.g. sample size, likely recruitment and drop-out rates) for future RCTs.

## Clinical Implications

The primary clinical implication of this study is that, should sling use be found to reduce postnatal depression scores, then this lends evidence to the effectiveness of sling use as a possible early intervention for post-natal depression, perhaps reducing both the prevalence and impact of this condition.

## Aims and Hypotheses

A feasibility study is underpowered to reliably assess treatment effectiveness (Williams, 2016). Therefore the primary focus of a feasibility study is not hypothesis testing, though statistical analysis of between-group outcome differences may be conducted in a preliminary way in order to inform the sample size calculations of future RCTs (Williams, 2016). Instead, as a feasibility study, the focus of this study is on collecting information that will support the design of future studies, e.g. recruitment rates, treatment adherence etc.

The primary aim of this study is therefore to examine whether it is possible to conduct an RCT with this population (mothers of new-born infants) and intervention (sling use, training and support). This study has a particular focus around the feasibility of recruitment of this population and also around treatment fidelity, including whether control group participants independently engage in sling use during the trial.

While this study is underpowered to draw definitive conclusions around treatment effectiveness, it is predicted that sling use will lead to lower Postnatal Depression scores (as measured by the Edinburgh Postnatal Depression Scale (Cox, Holden, & Sagovsky, 1987), and higher wellbeing scores (as measured by the Warwick Edinburgh Mental Wellbeing Scale (WEMWBS); Tennant et al., 2007), parenting self-efficacy and responsiveness (as measured by the Parenting Sense of Competency Scale (PSCS); Gibaud-Wallston & Wandersman, 1978; and Caregiving Experiences Questionnaire (CEQ); Brennan, George & Solomon, 2013), and breastfeeding frequency and duration, in the intervention group, compared to the control group. It is predicted that any improvement seen in the scores on these measures post-intervention, in comparison to pre-intervention scores, will be significantly greater for intervention group participants, than any improvement seen for control group participants.

A secondary hypothesis is that maternal attachment style (as measured by the Experiences in Close Relationships Scale-Short (ECR-S; Wei, Russell, Mallinckrodt & Vogel, 2007) might act as a moderator of the relationship between sling use and the scores on these various measures.

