### *Parenting*

The Parenting Sense of Competency Scale (PSCS; Gibaud-Wallston & Wandersman, 1978)(Appendix J) will be used to measure parental self-efficacy. This scale measures two dimensions of parental competence: Satisfaction and Efficacy. It is a 16-item likert-scale questionnaire in which participants give responses ranging from “strongly agree” (1) to “strongly disagree” (6). There are nine questions for the dimension of Satisfaction (examining the parents’ perceived anxiety, motivation and frustration), and seven assessing Efficacy (parents’ perceived competence, capability and problem-solving abilities). This scale has been validated (Ohan, Leung, & Johnston, 2000).

Following the example of Cutrona & Troutman (1986), and again, following feedback from service users, this study may, for the sake of brevity, use only the seven Efficacy items.

The Caregiving Experiences Questionnaire (CEQ; Brennan, George & Solomon, 2013) will also be used as a parenting measure within this study, assessing the nature of each participating mother’s relationship with their child. The CEQ is a measure designed to assess 5 dimensions of the parent-child relationship. These dimensions have emerged from attachment theory and include “enjoyment, discourages closeness, heightened, helplessness, and role reversal” (Brennan et al., 2013). Each item of this scale is a statement designed to examine a mother’s evaluations of themselves, their child, and their relationship with their child. Altogether the CEQ contains 40 of these statements (Appendix K), with mothers asked

to endorse items using a five-point Likert scale ranging from “Not at all characteristic” (1) to “Very characteristic” (5). The CEQ was developed and validated in a US population.

Research investigating the validity of this measure in non-US populations is ongoing (Røhder et al., 2018).

Lastly, a measure of infant stroking by mothers has been included in the battery of questionnaires. This is because recent literature has highlighted possible associations between maternal mental health and maternal stroking (Sharp, Pickles, Meaney, Marshall, Tibu, & Hill, 2012). A measure developed by Sharp et al. (2012), which was designed for use in the community, will be used in this study also (please see Appendix N).

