### *Breastfeeding*

Information will be collected around mothers’ feeding methods (i.e. whether they are breastfeeding or tend to formula feed) over the course of the study. This breastfeeding item has been integrated into the demographics questionnaires, but, unlike the demographic questions, will be re-administered at the final data collection time-point (Please see Appendix O).

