### *Data Collection*

When their infant is 0 to 6 weeks old participants will complete baseline measures. For intervention participants completion of baseline measures will be prior to attending the sling surgery session. Currently these are due to include measures of PND (EPDS, DASS21), attachment (ECR-S), a measure of sling and buggy use and also of use of sling surgery services, a breastfeeding measure, and measures of wellbeing (WEMWBS/SWEMWBS), parenting (PSCS, CEQ), infant temperament (IBQ-R VSF) perceived social support (SPS) and general demographics (as mentioned in the *participants* section above).

As part of this feasibility study, it would be helpful to examine how long is needed before an effect of sling use upon maternal mental health, wellbeing and parenting may be seen. This information could support future RCTs in deciding the duration of a sling use intervention condition. It was agreed that an additional time-point, midway through the study, may help to narrow down the point at which an effect of sling use may be seen. Thus, 6 weeks

after completion of baseline measures, both intervention and control participants will be asked (via text or email - see below) to complete Time-2 (T2) measures online. These T2 measures are not the full battery of measures. Rather, participants in both groups will be asked about current sling use and use of sling surgery services (including whether they have swapped their sling). The EPDS will also be administered a second time at this time-point.

A further 6 weeks later (T3) participants in both conditions will be asked (via text or email - see below) to complete for a second time the full battery of measures that had been given at baseline (T1) (excluding demographic measures).

A text or email reminder (depending on each participant's stated preferred method of contact) will be sent each time that the participant is due to complete their next battery of measures. This message will contain a link to these measures (via Qualtrics).

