## Appendix J Parenting Sense of Competency Scale (PSCS; Gibaud-Wallston & Wandersman, 1978)

| Please rate the extent to which you agree or disagree with each of the following statements.                                                    |                      |          |       |                   |                   |             |
|-------------------------------------------------------------------------------------------------------------------------------------------------|----------------------|----------|-------|-------------------|-------------------|-------------|
| Strongly
Disagree                                                                                                                            | Somewhat
Disagree | Disagree | Agree | Somewhat
Agree | Strongly
Agree |             |
| 1                                                                                                                                               | 2                    | 3        | 4     | 5                 | 6                 |             |
| 1. The problems of taking care of a child are easy to solve once you know how your actions affect your child, an understanding I have acquired. |                      |          |       |                   |                   | 1 2 3 4 5 6 |
| 2. Even though being a parent could be rewarding, I am frustrated now while my child is at his / her present age.                               |                      |          |       |                   |                   | 1 2 3 4 5 6 |
| 3. I go to bed the same way I wake up in the morning, feeling I have not accomplished a whole lot.                                              |                      |          |       |                   |                   | 1 2 3 4 5 6 |
| 4. I do not know why it is, but sometimes when I'm supposed to be in control, I feel more like the one being manipulated.                       |                      |          |       |                   |                   | 1 2 3 4 5 6 |
| 5. My mother was better prepared to be a good mother than I am.                                                                                 |                      |          |       |                   |                   | 1 2 3 4 5 6 |

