**Other ethnic group**

- ☐ Arab  
☐ Any other ethnic group, please describe:

**Is your child your....?**

- ☐ Firstborn  
☐ Second born  
☐ Third born  
☐ Fourth born  
☐ Fifth born +

Would you like to provide any further information?

.....  
.....

**How do you feed your baby?** (We're interested in their milk feeds only, not solids)

- ☐ Formula feed  
☐ Breastfeed  
☐ Both formula feed and breastfeed

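### Breastfeeding frequency and duration are predicted outcomes, but the only feeding item records method at T1 and T3; separately, the PSCS anchors run in opposite directions in the Measures text and on the form

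*Protocol*

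**What the plan says.** **Breastfeeding.** Among the predictions in Aims and Hypotheses is higher "breastfeeding frequency and duration, in the intervention group, compared to the control group". The Breastfeeding paragraph under Measures describes the information to be collected as feeding method, that is "whether they are breastfeeding or tend to formula feed". It places the item in the demographics questionnaire and repeats it at the last time-point. Appendix O holds the item itself: "How do you feed your baby", with the note "We're interested in their milk feeds only, not solids". The three answers are formula feeding, breastfeeding, and "Both formula feed and breastfeed". Data Collection lists a breastfeeding measure at baseline and restricts T2 to sling use, use of the sling service and the EPDS. The Appendix B items for all time points contain no feeding question.

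**PSCS.** The Parenting paragraph under Measures says: "It is a 16-item likert-scale questionnaire in which participants give responses ranging from" strong agreement, given the value 1, to strong disagreement, given the value 6. It adds that only the seven Efficacy items may be used. The form in Appendix J opens with "Please rate the extent to which you agree or disagree with each of the following statements" and prints its anchors from Strongly Disagree at 1 to Strongly Agree at 6. Aims and Hypotheses predicts higher parenting self-efficacy, as measured by the PSCS, in the intervention group.

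**The concern.** These are two unrelated defects, and each can be checked within the protocol.

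In the first, a hypothesis names two quantities and the instrument measures neither directly. No analysis plan can repair this later, because the answers are never asked for. The study exists to supply parameters for a future trial. As designed it can supply no estimate or standard deviation for feed frequency, and only a crude one for duration.

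In the second, two pages of the same document give incompatible codings for one scale. The predicted direction is towards higher self-efficacy, so the coding has to be unambiguous for the reported sign to be read correctly.

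**Working it through.** The protocol gives no figure to reproduce here. The check sets its statements side by side and works out what each implies.

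**Breastfeeding**

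1. Timing: T1 is at infant age 0 to 6 weeks. T2 follows 6 weeks later and T3 a further 6 weeks later, so T1 to T3 is 6 + 6 = 12 weeks and T3 falls at about 12 to 18 weeks of age.
2. Frequency: the item is a present-tense question with three method categories. None of them holds a count, so the number of feeds cannot be derived at either time-point.
3. Duration, by pattern of answers:
   - Breastfeeding (alone or with formula) at T1, formula only at T3: she stopped somewhere in a 12-week window. A woman stopping the day after T1 and one stopping the day before T3 give identical answers, although their durations differ by 84 - 2 = 82 days.
   - Still breastfeeding at T3: duration is censored at 12 to 18 weeks.
   - Formula only at T1: any earlier breastfeeding is of unknown length.
4. What the item does give: any breastfeeding (breast or both) against none, and breast only against the rest, at two time-points 12 weeks apart.

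**PSCS**

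1. Items are scored 1 to 6, so swapping the anchors maps an item score s to 7 - s.
2. Seven Efficacy items (range 7 to 42): total x becomes 7 × 7 - x = 49 - x.
3. Sixteen items (range 16 to 96): total x becomes 7 × 16 - x = 112 - x. The same holds when the nine Satisfaction items are reverse-scored. With E and S the raw sums under the form coding, the composite is C = E + (63 - S). With the anchors swapped and the same scoring rule it is (49 - E) + S = 112 - C.
4. Illustration: an assumed gain of 0.5 per item on seven items is 0.5 × 7 = +3.5 under the form coding and -3.5 under the text coding.
5. Item wording: items 1, 6, 7, 10, 11, 13 and 15 are positively worded and the other nine are negatively worded. This matches the seven Efficacy and nine Satisfaction items that the protocol counts, although it does not assign items to subscales. On that reading, a higher Efficacy total means more self-efficacy under the form coding. Under the text coding it does so only after reversal.
6. The printed anchors run Strongly Disagree, Somewhat Disagree, Disagree, Agree, Somewhat Agree, Strongly Agree. The two Somewhat labels therefore sit further out than plain Disagree and Agree, which is not an ordered scale.

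**The case against.** The strongest reply is that little hangs on either point. The protocol says that hypothesis testing is not its primary focus and that it is underpowered for effectiveness. Breastfeeding is the last outcome in its list of predictions. T2 was kept short deliberately, and questionnaire burden is a stated worry. All of this stands. It limits the weight of the point and favours rewording the hypothesis over adding items.

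Three stronger readings are tempting, and the protocol does not support them.

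- A reader might infer that there is no information on duration at all. That goes too far: the item shows whether breastfeeding has lasted to about 12 to 18 weeks, brackets stopping for some women, and gives a crude exclusivity category.
- A reader might infer that a mixed ANCOVA is to be run on a three-category answer. Proposed Analysis applies that model to maternal mental health, wellbeing and parenting and does not name breastfeeding. How the item is analysed may properly be left to the analysis plan.
- A reader might infer that a benefit on self-efficacy would be reported as harm. The Parenting paragraph describes response options and is not a scoring algorithm. The sign would flip only if an analyst coded the completed forms by the contrary text, ignoring both the labels on the form and the direction stated in the hypotheses.

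It can also be said that reverse-scoring rules belong in an analysis plan. That is fair for the detail, but such a plan would leave the two pages of the protocol in contradiction.

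**Conclusion.** Both points hold, at modest weight. For breastfeeding, the stated hypothesis and the stated instrument do not match: frequency cannot be estimated, and duration is known at best to within about 12 weeks. This assumes that the Appendix O question is the only feeding item and that it is asked at T1 and T3, as the protocol's schedule and forms show.

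For the PSCS, the text and the form contradict each other and must be reconciled. The contradiction is complete in direction (49 - x on seven items, 112 - x on sixteen), but it is a potential error in scoring, not a demonstrated one. The 49 - x figure applies only if the seven-item option is taken up.

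Neither point touches recruitment, treatment fidelity, the EPDS or the primary feasibility aim. Both should be corrected because the outcomes are named in the hypotheses and are meant to inform a later trial.

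**What to change.** **Breastfeeding, preferred:** restate the hypothesis as any (or exclusive) breastfeeding at T3, as a difference in proportions between groups with a 95% CI, taking account of T1 feeding. Exclusive here can mean only no formula, since the item asks about milk feeds alone. This costs one sentence and adds no burden. With 25 to 30 women per group the interval will be wide and should be presented as descriptive.

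**Breastfeeding, alternative:** keep frequency and duration, and add two short items: breastfeeds in the past 24 hours, and infant age when breastfeeding stopped. The cost is slightly more questionnaire time, to be weighed against the protocol's concern about burden.

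**PSCS:** correct the Parenting paragraph to the coding on the form participants complete (1 = strongly disagree, 6 = strongly agree). State that negatively worded items are reversed so that a higher score means greater competence. Check the order of the Somewhat labels on the form at the same time, so that the text is not aligned to a disordered scale. This costs one or two lines of text and a check of the online form before it is issued.
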